**Primary outcome measures**				
Psychological distress	Symptom Checklist 90 (90 items)	5 point Likert scale	During the past 7 days about how much were you distressed or bothered by:	T0; T1; T2; T3
				
	· Anxiety (10 items)	* range 90–450	*Feeling fearful (anx)	
	· Agoraphobia (7 items)			
	· Depression (16 items)		* Feelings of worthlessness (depr)	
	· Somatisation (12 items)		* Numbness or tingling in parts of your body (som)	
	· Obsessive-compulsive behaviour (9 items)			
	· Interpersonal sensitivity (18 items)		* Feeling that people are unfriendly of dislike you (int.sens)	
	· Hostility (6 items)		* Nervousness or shakiness inside (anx)	
	· Sleep (3 items)			
Psychological empowerment	Cancer Empowerment Questionnaire (40 items)	5 point Likert scale		T0; T1; T2; T3
	· Personal strength (19 items)	* range 40-200	* I know what I am good at (pers.str)	
	· Social support (9 items)		* The people around me take me for who I am (soc.sup)	
	· Community (6 items)		* In our society people with breast cancer are considered wholly (com)	
	· Health care (6 items)		* My health care professionals are there when I need them (h.care)	
**Secondary outcome measures**				
Anxiety and depressive states	Hospital Anxiety and Depression Scale (14 items)	4 point Likert scale	During the past week:	T0; T1; T2; T3
				
	· Anxiety (7 items)	* range 0-21 (subscales)	* I am restless and can’t keep still (anx)	
	· Depression (7 items)	* range 0-42 (total)	* I feel miserable and sad (depr)	
Breast cancer- related quality of life	EORTC-C30 (30 items)	4 point Likert scale	During the past week:	T0; T1; T2; T3
				
	· Functional scales (physical, role, emotional, social, and cognitive functioning - 15 items)	* range 15-60	* Has your physical condition interfered with your family life? (role.func)	
	· Symptom scales (fatigue, pain, nausea/vomiting - 7 items)	* range 7-28	* Have you had difficulties remembering things? (cog.func)	
	· Single symptom items (6 items)	* range 6-24 7-point linear analogue scale; range 2-14	* Did pain interfere with your daily activities? (pain)	
	· Global health and global quality of life (2 items)		* How would you rate your overall quality of life during the past week?	
	EORTC-BR23 (23 items)	4 point Likert scale	During the past week:	T0; T1; T2; T3
				
	· Functional scales (body image, sexual functioning, sexual enjoyment, future perspective - 8 items)	* range 8-32	* Did you find it difficult to look at yourself naked? (body.im)	
	· Symptom scales (arm symptoms, breast symptoms, systemic therapy side effects, upset by hair loss - 15 items)	* range 15-60	* Did you have a swollen arm or hand? (arm.symp) During the past 4 weeks:	
			* To what extent were you interested in sex? (sex.enj)	
General distress	Distress Thermometer (1 item)	11 point Likert scale		T0; T1
		* range 0-10	* Circle the number that best describes how much distress you have been experiencing in the past week including today.	
Remoralization	Remoralization Scale (12 items)	4 point Likert scale		T0; T1
		* range 12-48	* I am in control of my life	
			* I take a positive attitude toward myself	
Personal control	Mastery scale (7 items)	5 point Likert scale		T0; T1; T2; T3
		* range 7-35	* What happens to me in the future mostly depends on me	
Positive adjustment to cancer	Positive Adjustment Questionnaire (39 items)	1-7 scale	Since you found out about your illness:	T0; T1; T2; T3
				
	· Fulfilment (9 items)	* range 9-63	* My life is not limited by my illness (ful)	
	· Re-evaluation (9 items)	* range 9-63	*I see life differently (re-ev)	
	· New ways of living (10 items)	* range 10-70	* I can take things more in my stride (new.w)	
	· Valuing life (7 items)	* range 7-49	* I value life a lot more now (val)	
Coping with the experience of cancer	Impact of Event Scale	4 point Likert scale		T0; T1
	· Intrusion (7 items)	* range 13-52	* I had dreams about it (intr)	
		· Avoidance (8 items)	* I tried not to think about it (avoid)	
			* I tried not to talk about it (avoid)	
	Brief COPE (28 items)	4 point Likert scale		T0; T1
	· Active coping (2 items)	* range 0-6 (subscales)	* I’ve been taking action to try to make the situation better (act.cop)	
	· Planning (2 items)		* I’ve been learning to live with it (acc)	
	· Positive reframing (2 items)		* I’ve been giving up to attempt to cope (behav.dis)	
	· Acceptance (2 items)			
	· Humor (2 items)			
	· Religion (2 items)			
	· Using emotional support (2 items)			
	· Using instrumental support (2 items)			
	· Self-distraction (2 items)			
	· Denial (2 items)			
	· Venting (2 items)			
	· Substance use (2 items)			
	· Behavioral disengagement			
			* I’ve been criticizing myself (self-bl)	
	· (2 items)			
	· Self-blame (2 items)			
Self-efficacy	Self Efficacy Scale (7 items)	4 point Likert scale		T0; T1
		* range 7-28	* Whatever I do, I cannot change my complaints	
			* I think I could positively influence my complaints	
Fear of cancer recurrence	Cancer Worry Scale (8 items)	4 point Likert scale	During the past month:	T0; T1; T2; T3
				
				
		* range 8-32	* How often have you thought about your chance of getting cancer (again)?	
			* Have these thoughts affected your mood?	
	Cancer Acceptance Scale (2 items)	4 point Likert scale		T0; T1
		* range 2-8	* I worry about the cancer returning	
			* I am anxious about my health	
Fatigue Severity	Checklist Individual Strength	7-point Likert scale		T0; T1; T2; T3
	· subscale Fatigue Severity (8 items)	* range 8-56	* I feel tired	
			* I am rested	
			* Physically I feel exhausted	
Family communication	ODHCF (14 items)	5 point Likert scale		T0; T1; T2; T3
	· Nuclear family (7 items)	* range 7-35 (subscales) (or less if not applicable; no partner/ children/ parents/ siblings)	* My partner doesn’t (nucl.fam) / parents don’t (fam.or) want me to talk about breast cancer	
	· Family of origin (7 items)		* My children (nucl.fam) / siblings (fam.or) often don’t know what to say or do, when I’m feeling down because of breast cancer.	
Illness perceptions	Illness Cognition Questionnaire (18 items)	4 point Likert scale		
	· Helplessness (6 items)	* range 6-24 (subscales)	* My illness controls my life (help)	T0; T1; T2; T3
	· Acceptance (6 items)		* I can accept my illness well (acc)	
	· Perceived benefits (6 items)		* I have learned a great deal from my illness (perc.ben)	
Personality	Big Five Inventory (44 items)	5 point Likert scale	I see myself as someone who:	T0; T1
	· Neuroticism (8 items)	* range 1-5 (subscales)	* Worries a lot (neu)	
	· Extraversion (8 items)		* Is full of energy (ext)	
	· Openness to experience (10 items)		* Tends to be disorganized (con)	
	· Conscientiousness (9 items)		* Is considerate and kind to almost everyone (agr)	
	· Agreeableness (9 items)			
Health care utilization	Trimbos/iMTA questionnaire for Costs associated with Psychiatric illness (TiC-P)		Since completion of primary curative breast cancer treatment (T0) / In the past four months (T1; T3) / In the past two months (T2):	T0; T1; T2; T3
	· Contacts with medical or mental health care professionals (14 items)	Yes/no; frequency	* Did you visit a psychologist? (con)	
	· Hospitalization (1 item)	Yes/no; reason Yes/no; dose and frequency	* Did you use antidepressants? (med)	
	· Use of breast cancer- specific, psychiatric and other medication (8 items)	Yes/no; costs	* Did you take part in a breast cancer rehabilitation program? (other)	
	· Other costs (10 items)			

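### Table 2 implies that the family communication (ODHCF) score is an unprorated sum that falls with the number of living or existing relatives; separately, the Impact of Event Scale range does not fit its listed items

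*Protocol article*

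**What the plan says.** Both entries are in Table 2 of the protocol article, under the secondary outcome measures.

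- **Family communication.** The entry reads "ODHCF (14 items"), split into "Nuclear family (7 items") and "Family of origin (7 items"), on a "5 point Likert scale". The subscale range is 7 to 35, followed by the note "or less if not applicable; no partner/ children/ parents/ siblings". It is measured at T0, T1, T2 and T3. The Secondary outcomes section says that the scale was modified for this population and does not describe how the modified version is scored.
- **Impact of Event Scale.** The entry lists "Intrusion (7 items") and "Avoidance (8 items"), on a "4 point Likert scale", with a printed range of 13 to 52. It is measured at T0 and T1.

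The Statistical analysis section names a model only for the two primary outcomes, distress and empowerment.

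**The concern.** The range note on the ODHCF says that a subscale total gets smaller when a relative does not exist. That happens if the answers are added up with no allowance for items that do not apply. A woman without a partner or children would then score lower on openness within the nuclear family because fewer answers are added, not because her family talks less. Family composition and openness would be mixed in one number. What is at stake is the precision and interpretability of one secondary outcome.

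The Impact of Event Scale entry is a different and smaller matter: its item counts and its range cannot both be right.

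**Working it through.** **Rule used.** A sum of k items with lowest code a and highest code b runs from k × a to k × b.

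**Reproducing the printed ranges.** For the ODHCF, 7 × 1 = 7 and 7 × 5 = 35, which is the printed 7 to 35. With codes that start at 0 or 1, the same rule reproduces all 15 Table 2 ranges that were checked, among them the SCL-90 (90 × 1 to 90 × 5 = 90 to 450), the CEQ (40 to 200), the Cancer Worry Scale (8 to 32) and the ODHCF itself. The Impact of Event Scale was the only other entry tried, and it failed.

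**What the ODHCF note implies.** Three scoring rules can be set against it, for a woman with k applicable items out of 7:

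| Rule | Possible range | Falls when relatives are absent? |
|---|---|---|
| Plain sum | k to 5k | yes |
| Prorated sum, 7 × (sum / k) | 7 to 35 | no |
| Mean of applicable items | 1 to 5 | no |

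Only the plain sum agrees with a range that drops below 7 to 35. The same table prints a mean-type range where one applies: the Big Five Inventory has 8 to 10 items per subscale and a subscale range of 1 to 5.

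**Size, under the plain sum.** The values of k are assumed, because the article does not say how many items concern partner, children, parents or siblings.

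| k | Range | Sum if every answer is 3 | Change in sum if every answer moves by 1 | Mean of applicable items if every answer is 3 |
|---|---|---|---|---|
| 7 | 7 to 35 | 21 | 7 | 3.0 |
| 5 | 5 to 25 | 15 | 5 | 3.0 |
| 4 | 4 to 20 | 12 | 4 | 3.0 |
| 3 | 3 to 15 | 9 | 3 | 3.0 |

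Between k = 7 and k = 4 the gap at identical answers is 21 − 12 = 9 points, on a full span of 35 − 7 = 28. Comparison with baseline removes the difference in level while k stays fixed, but not the scaling: a woman with k = 4 contributes 4/7 of the change that a woman with k = 7 contributes for the same shift per item. If k itself changes between T0 and T3, the sum moves with no change in openness.

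**Impact of Event Scale.** Listed items: 7 + 8 = 15.

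- Codes 1 to 4: 15 × 1 = 15 to 15 × 4 = 60.
- Codes 0 to 3: 15 × 0 = 0 to 15 × 3 = 45.
- To reach 13 to 52 with 15 items, the codes would have to be 13/15 = 0.87 and 52/15 = 3.47, which are not integers.
- The printed range fits 13 items coded 1 to 4: 13 × 1 = 13 and 13 × 4 = 52.

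The numeric codes are not stated. Both conventions occur in the table for four-point scales: Brief COPE subscales (2 items, 0 to 6) and HADS subscales (7 items, 0 to 21) are coded 0 to 3, and the Cancer Worry Scale (8 items, 8 to 32) is coded 1 to 4.

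**The case against.** The article writes out no scoring algorithm for the ODHCF. The note is in a column headed response format, and that column does not always define analysis scores: it gives one pooled range of 15 to 60 for five EORTC functional scales. The handling of items that do not apply is commonly left to the full protocol or the analysis plan, neither of which is shown, and either may prorate. This stands to the extent that the plain sum is an inference, and the lack of a proration rule is not itself a finding. What remains is that the printed range agrees with a plain sum and with neither alternative.

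A reader might infer that the scoring biases the treatment comparison. The document does not support that. Family structure mostly precedes randomisation, so it is balanced between arms in expectation. Stable differences in level can largely be absorbed by comparison with baseline, and no frequency of family changes over the 10 months is given. The remaining effects are added variance, levels that cannot be compared between women, and change scaled by k.

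A reader might also infer that the Impact of Event Scale will be mis-scored, or that 15 to 60 is the correct range. Neither follows. A misprinted range does not alter how answers are summed, 0 to 45 is equally open, and the item counts could be the part in error. The table layout is broken at this row in the text as read, but that does not change the figures 7, 8, 13 and 52.

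**Conclusion.** The point holds at a minor level. As printed, the ODHCF range implies an unprorated sum from k to 5k, so that level and size of change depend on family composition. In the illustration, identical answers score anywhere from 21 down to 9 as k goes from 7 to 3. This rests on two assumptions: that the note reflects the intended scoring, and the illustrative values of k. The cost is lost precision and comparability on one secondary outcome, not bias between arms.

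The Impact of Event Scale entry contradicts itself: 15 listed items cannot give 13 to 52. This is a table-level inconsistency, and the document does not show which part is wrong.

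Neither scale enters the sample size calculation, which is based on the SCL-90, or the primary analysis.

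**What to change.** 1. Score each ODHCF subscale as the mean of the applicable items (1 to 5), set it to missing below a prespecified minimum number of applicable items, and replace the range note in Table 2 accordingly. If the full protocol or analysis plan already prorates, only the note needs correcting.
2. Reconcile the Impact of Event Scale entry: confirm the number of items administered and the response codes, then correct either the item counts or the range.

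The cost is one scoring line and a table correction, with no new data. The small downside is that scores based on very few items are less reliable, or are missing once the minimum is applied.

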### Statistical analysis

A general linear model for repeated measurements (by the method of mixed linear model) will be used to analyze the effect of the BREATH intervention on the two primary outcome variables (distress and empowerment). Chi square (categorical variables), ANOVA (normally distributed continuous variables), and Kruskall-Wallis (non-parametric variables) will be used to asses baseline characteristics between groups. Analysis will be done according to intention-to-treat methodology.

### Time line of the BREATH study

Recruitment of participants began in 2010. Primary end-points (baseline T0 and post-intervention T1) and all follow-up measures (T2-T3) are expected to be completed in January 2013.

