**Methods/design:**

The non-guided Internet-based self-management intervention is based on cognitive behavioural therapy techniques and covers four phases of recovery after breast cancer (Looking back; Emotional processing; Strengthening; Looking ahead). Each phase of the fully automated intervention has a fixed structure that targets consecutively psychoeducation, problems in everyday life, social environment, and empowerment. Working ingredients include Information (25 scripts), Assignment (48 tasks), Assessment (10 tests) and Video (39 clips extracted from recorded interviews). A non-blinded, multicentre randomised controlled, parallel-group, superiority trial will be conducted to evaluate the effectiveness of the BREATH intervention. In six hospitals in the Netherlands, a consecutive sample of 170 will be recruited of women who completed primary curative treatment for breast cancer within 4 months. Participants will be randomly allocated to receive either usual care or usual care plus access to the online BREATH intervention (1:1). Changes in self-report questionnaires from baseline to 4 (post-intervention), 6 and 10 months will be measured.

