### Study design

This study is designed as a non-blinded, multicentre randomised controlled, parallel-group trial evaluating the superiority of the BREATH intervention compared to usual care after primary curative breast cancer treatment. A consecutive sample of 170 BCS from 6 hospitals will be evaluated in this RCT. Baseline measure (T0) and randomization take place 3 months after completion of primary curative breast cancer treatment. This starting point was chosen because this is in accordance with the standard first follow-up visit after completion of primary treatment as described in the Dutch national breast cancer guideline. Moreover, these 3 months allow for the natural recovery of emotional well-being and adjustment to take place. After completion of baseline measure, participants will be randomised to either intervention or control group. Follow-up measures are respectively 4 months (T1; post-intervention), 6 months (T2), and 10 months (T3) after baseline. The overall study design is captured in Figure 
1.

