### Sample size calculation

Based on the two primary outcomes of the BREATH study, effect on patient level is defined as a decrease in psychological distress (as measured with the SCL-90) *or* an increase in empowerment (as measured with the CEQ). Therefore, effectiveness of the BREATH intervention is demonstrated when one of the two effects is significant. Sample size calculation is based on the SCL-90, since the SCL-90 has proven sensitive to change through psychological face-to-face intervention in fatigued cancer survivors 
[36] and information on sensitivity to change of the CEQ is unknown. Significance level of the sample size calculation was adjusted to p ≤ 0.25 to keep the overall chance for type-I errors on 5%. To detect a significant difference (0.25) with 80% power between intervention and control group on the SCL-90, a sample size of 128 BCS (64 in each group) is needed. This sample size calculation is based on a medium effect size of 0.50 of the BREATH intervention, which has proven to be a high effect size for non-guided psychological interventions 
[74]. Based on a systematic review on attrition in randomised controlled trials of Internet interventions for anxiety and depression 
[75], we take into account a 25% study drop-out rate. This results in a maximal sample size of 170 BCS that need to be included in the BREATH trial in case of considerable drop-out.

**Table 2 T2:** Primary and secondary outcome measures of the BREATH study

**Questionnaires**		**Response format**	**Example questions**	**Timepoints**

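### The deciding test is not tied to T1, and the natural reading makes it a change-from-baseline contrast, which is less precise than a baseline-adjusted T1 comparison

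*Protocol article*

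**What the plan says.** Four places in the protocol article bear on which comparison decides the trial.

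- **Time line of the BREATH study** is the only place that calls a time point primary: "Primary end-points (baseline T0 and post-intervention T1) and all follow-up measures (T2-T3) are expected to be completed in January 2013". T2 and T3 appear there as follow-up.
- **Statistical analysis** gives the method for distress (SCL-90) and empowerment (CEQ): "A general linear model for repeated measurements (by the method of mixed linear model) will be used to analyze the effect" of the intervention on both. It does not say which waves enter, which term is tested, or whether T0 is a response or a covariate.
- **Sample size calculation** rests on a single contrast: "To detect a significant difference (0.25) with 80% power between intervention and control group on the SCL-90". The assumed standardised effect is 0.50, and the result is that "a sample size of 128 BCS (64 in each group) is needed". No time point and no within-person correlation is given. The same section sets the success rule: "effectiveness of the BREATH intervention is demonstrated when one of the two effects is significant".
- **Study design** and the **Abstract** give the schedule without singling out a wave: "Follow-up measures are respectively 4 months (T1; post-intervention), 6 months (T2), and 10 months (T3) after baseline", and "Changes in self-report questionnaires from baseline to 4 (post-intervention), 6 and 10 months will be measured". Table 2 lists both primary outcomes at T0, T1, T2 and T3.

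**The concern.** The time point labelled primary, the comparison that was sized and the effect that is tested stand in three sections, and nothing links them. The success rule counts two effects, one per outcome, and splits the error between them. That split is easiest to defend when each outcome has exactly one named test.

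Precision is also at stake. If the time line and the analysis section are read together, T0 and T1 are repeated responses in one model, and the intervention effect is the group-by-time term: the difference between arms in change from T0 to T1. In a randomised trial the arms have equal expected scores at baseline, and that analysis does not use this knowledge. Conditioning on T0, or constraining the arm means to be equal at T0, answers the same question with a smaller variance.

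**Working it through.** **Inputs from the article.** 64 per arm; standardised effect 0.50; 80% power; 1:1 allocation; two primary outcomes with an overall type-I error of 5%.

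**Assumptions.** The article prints a significance level of 0.25. Half of 5% is 0.025, so I use two-sided 0.025 and show two-sided 0.05 beside it. The T0-T1 correlation ρ is not given, so I show 0.3 to 0.8. I assume equal variances at T0 and T1 and complete data on 64 per arm.

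**The plan's own figure.** For a plain two-group comparison, n per arm = 2(z₁₋α/₂ + z₀.₈₀)² / 0.50².

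- Two-sided 0.05: 2(1.960 + 0.842)² / 0.25 = 62.8, so 63. The exact t-test gives 63.77, so 64 per arm and 128 in total, which matches the article.
- Two-sided 0.025: 2(2.241 + 0.842)² / 0.25 = 76.0, so 77 per arm and 154 in total (156 by t-test).
- Two-sided 0.25, as printed: 64 in total.

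So 128 is the size for one ordinary two-group comparison at two-sided 0.05 (or one-sided 0.025), with no repeated-measures parameter in it. The mismatch in the significance level is a separate matter and is not used as support here.

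**Two ways to estimate the T1 effect.** In units of 2σ²/n, the variance of the arm difference is:

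- T1 score alone: 1
- change from T0 to T1 (T0 as a free response): 2(1 − ρ)
- T1 given T0 (covariate, or equal arm means at T0): 1 − ρ²

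The ratio of the last to the second is (1 − ρ²) / [2(1 − ρ)] = (1 + ρ)/2, which is below 1 for any ρ < 1.

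**Power.** For T1 alone, 0.50 / √(2/64) = 2.828. Divide this by the square root of the variance factor, subtract the critical value (2.241 at 0.025, 1.960 at 0.05) and take the normal probability.

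- ρ = 0.5, change: 2.828/√1.00 − 2.241 = 0.587, power 72.1%
- ρ = 0.5, adjusted: 2.828/√0.75 − 2.241 = 1.025, power 84.7%
- ρ = 0.7, change: 2.828/√0.60 − 2.241 = 1.410, power 92.1%
- ρ = 0.7, adjusted: 2.828/√0.51 − 2.241 = 1.719, power 95.7%

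| Assumed ρ | 2(1 − ρ) | 1 − ρ² | Change, 0.025 | Adjusted, 0.025 | Change, 0.05 | Adjusted, 0.05 |
|---|---|---|---|---|---|---|
| 0.3 | 1.40 | 0.91 | 55.9% | 76.5% | 66.7% | 84.3% |
| 0.5 | 1.00 | 0.75 | 72.1% | 84.7% | 80.7% | 90.4% |
| 0.6 | 0.80 | 0.64 | 82.1% | 90.2% | 88.5% | 94.2% |
| 0.7 | 0.60 | 0.51 | 92.1% | 95.7% | 95.5% | 97.7% |
| 0.8 | 0.40 | 0.36 | 98.7% | 99.3% | 99.4% | 99.7% |

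For reference, T1 alone gives 72.1% at 0.025 and 80.7% at 0.05.

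In patients: at ρ = 0.5 the ratio is 0.75, so the adjusted contrast reaches with 0.75 × 64 = 48 per arm the precision that the change contrast reaches with 64. At ρ = 0.7 the ratio is 0.85, or 0.85 × 64 ≈ 54 per arm.

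**The case against.** The case for leaving the text alone is substantial. A journal article condenses its protocol, and the model term, the contrast and the handling of baseline commonly sit in an analysis plan, which is not shown here. An unnamed contrast alone is therefore no error. A mixed model can deliver a T1 contrast. A model on T0 and T1 only would fit both the analysis section and the time line, and its group-by-time term is a single one-degree-of-freedom test. Analysing change is valid in a randomised trial, and the abstract itself speaks of changes. At a correlation of 0.5 or more, the change contrast is no worse than the plain comparison on which the trial was sized. The 72% at 0.5 equals the power of that plain comparison at 0.025, so its shortfall from 80% comes from the significance level and the sample size, not from the use of change.

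All of this stands, and it limits the point to precision and clarity. It does not remove the point, because the benign T0-T1 model is exactly the one in which T0 is a response and the change contrast is the test.

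A reader might infer more: that a four-wave model is planned, that the T1 comparison was powered and then left untested, that power falls to about 29-36%, or that the overall error reaches 9-13%. The article does not support these. It does not say how many waves enter, and its sample size section names no time point. The low power figures need a group effect averaged over baseline as well as an assumed effect that fades. The error figures need success to count at any wave on either outcome, which makes six tests. The article proposes neither; its success rule speaks of two effects.

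**Conclusion.** The point holds as an improvement in precision and clarity, not as a flaw in validity. The article labels T1 primary in one section and does not carry that label into the analysis or the sample size. On the reading that best fits its own text, the T1 effect would be estimated as a change contrast. Conditioning on baseline would raise power by about 13 percentage points at a correlation of 0.5 and by about 4 at 0.7, at two-sided 0.025. The gain is larger at lower correlations and nearly nil at 0.8.

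The size depends on the assumed correlation, on 64 evaluable women per arm and on an effect of 0.50 SD. The direction does not depend on the correlation, because (1 + ρ)/2 is below 1 throughout. That T0 enters as a response is inferred from the two sections together and is not stated outright. If an analysis plan not shown already conditions on T0, the precision gain is already secured and only the link to T1 remains to be written down.

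**What to change.** In Statistical analysis, name one deciding test for each primary outcome: the between-arm difference at T1 from the mixed model. Take T0 either as a covariate with the post-baseline scores as responses, or as a response with arm means constrained equal at T0. Label the T2 and T3 contrasts secondary. In Sample size calculation, state that the 0.50 difference refers to this T1 comparison.

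The cost is a few sentences. Table 2 already schedules both outcomes at every wave, so no visit, questionnaire or participant is added. With one test per outcome, the split of the 5% error over two effects has a definite meaning. The change should be fixed before outcome data are examined by arm.
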